### Sample size calculation

In order to assess the effectiveness of the StroCare intervention, the two prospective groups will include all patients insured with the health insurance BARMER who will be hospitalised in one of the three participating clinics over a period of 24 months for stroke treatment and have given their written consent. Previous studies showed moderate to large effects of similar interventions on health-related quality of life with standardized mean differences (Cohen’s *d*) between treatment and control groups ranging from 0.2 to 0.6 [8, 12]. We aim to identify a moderate effect (Cohen’s *d*=0.3) of the intervention on patient’s experienced health-related quality of life. With a power of 80% and an alpha error of 0.025 (adjusted for two primary endpoints, the two subscales of the PROMIS-10), a sample size of *N*=213 patients per group (426 in total) will be needed. Accounting for an expected dropout rate of 10% results in a necessary sample size of 235 per group (470 in total). In the past few years, approximately 600 patients insured with BARMER with a diagnosis of stroke were treated annually in the three participating clinics. In the planned time frame of 24 months we thus expect to enroll the planned number of 426 patients if 39% of 1200 participants participate.

For the qualitative interviews it is indicated that on average 12 interviews are sufficient to reach theoretical saturation [13]. Thus, the planned sample size of a maximum of 21 patients enrolled in the intervention group and 20 employees of different departments (doctors, nurses, and IT staff) represents a meaningful basis for the investigation of the experience gained during the implementation.

### Arms and interventions

#### StroCare intervention

The key element will be, on the one hand, improved cooperation between the various health care providers across sectoral boundaries (acute hospital, neurological rehabilitation, outpatient aftercare) and a health insurance company. In addition, optimized secondary prevention, risk factor control and risk adjustment in accordance with guidelines is going to be achieved by establishing a specific follow-up care offer at all participating neurological clinics. The StroCare intervention is a multicomponent procedure aimed at different persons and points of stroke care. Its main components are:
*Primary contact -* A study nurse of the department of Neurology of the UKE will contact the patient during primary acute stroke treatment. This nurse will be the responsible contact person for the patient for all medical questions for the next two years. The outpatient managed care will also be organised by the stroke nurse. Every three months for the following two years, the responsible stroke nurse maintains contact to the patient via telephone and every six months, arranges a consultation with the patient in the outpatient clinic including a check-up (ECG, blood samples) and a physical examination.*Outpatient managed care -* To achieve an well-structured outpatient care and to ensure regular follow-up appointments, the patients will be scheduled for a check-up and physical examination every six months at the respective acute clinic. The follow-up treatment will be performed by a study nurse and a neurologist experienced in stroke care and will comprise a neurological examination, carotid and intracranial ultrasound, evaluation of risk factors, and planning of further treatment.*Case Management -* In addition to establishing contact with a stroke nurse, each patient is assigned a case manager. The case manager acts on behalf of the health insurance company and the first contact is made during acute inpatient care. The case manager supports the patient regarding organisational issues, whereby the individual social situation is taken into account. In addition to care-relevant issues from the statutory health insurance system (like a request for classification of the degree of care), issues concerning the social nursing care insurance will also be addressed. The family, professional and financial situation, the housing situation and mobility factors, other health risk factors, and co-morbidities are taken into account by the case manager. Further non-medical context factors for patient-centered monitoring are, for example, existing responsibilities of the proxy and living wills, religious affiliation, private interests, and relevant biographical events. The Case Management should prevent disruptions between inpatient and outpatient care. It initiates and organizes seamless transitions.*Coverage of costs by the health insurance company -* By participating in StroCare, additionally to standard care costs are generated through study nurses, case manager, IT-portal, and neurological outpatient follow-up examinations in the UKE. These costs are paid by the insurance company as well as the standard care costs of neurological rehabilitation .*Electronical allocation of capacities (rehabilitation portal) -* Within StroCare an electronic rehabilitation portal will be implemented to speed up and secure a tailored referral to the five cooperating rehabilitation clinics. The portal is also meant to ensure efficient information transfer (medical reports, pictures, diagnostics) (see Fig. 2 for a comparison of the control and the intervention group).

**Fig. 2 Fig2:**
[figure not shown]
Placement allocation in usual care and in the StroCare intervention. **a** usual care: medical staff inquires separately by telephone for vacancies in rehabilitation clinics. **b** StroCare: all inquiries are forwarded to the rehabilitation clinics and back via electronical platform

**Fig. 3 Fig3:**
[figure not shown]
Outcome measures

The portal establishes a network between the acute care hospitals and rehabilitation clinics in order to enable a direct and fast exchange of information (see Fig. 2b). Through the rehabilitation portal a direct inquiry for available capacities can be placed by an employee of the acute hospital to the rehabilitation clinics. Employees of the rehabilitation clinics are able to register when and where vacancies for neurological rehabilitation are available. Once a suitable rehabilitation clinic for the patient is found, the according reports and images can be sent directly to the clinic via the rehabilitation portal. With this software, a seamless transition in treatment is supposed to be achieved, whilst the staff members administrative tasks are reduced.

#### Standard care

Patients allocated to the control group experience the usual stroke care. After initial treatment at an acute clinic, a request for rehabilitation to the health insurance company has to be submitted and approved. Afterwards a suitable clinic for a neurological or geriatric rehabilitation with available capacities has to be found. This may not be achieved immediately after initial stroke treatment by the differently focused acute therapists, and in addition, not every patient receives the rehabilitation treatment best suitable for her/him [3].

### Outcome measures

#### Effectiveness

In order to assess the effect of intervention, patient-reported outcomes will be surveyed measuring health-related quality of life (Fig. 3). They will be measured 12, and 24 months after baseline, using the questionnaire “Patient Reported Outcome Information System 10-Question Short Form” (PROMIS-10). The PROMIS-10 is a standardized questionnaire and consists of two scales measuring mental health and physical health [14], respectively, which will serve as the two primary outcomes. For evaluation of the PROMIS-10, at first a sum score and afterwards a t-score with standardized t-values is calculated. Reference of M ± SD= 50 ± 10 regards to a sample of healthy American subjects.

Additionally, the secondary outcome of depression and anxiety symptoms will be measured at all time points, using the “Patient Health Questionnaire-4” (PHQ-4) [15]. This questionnaire entails the two dimensions, depressive and anxiety symptoms, with two items each. The sum score ranges from 0 to 6 in each dimension. A score of 3 or higher indicates a potential anxiety or depression. The patient’s functional status will be assessed by the modified Rankin Scale questionnaire (smRSq) [16]. The scale of the smRSq ranges from 0 (“no symptoms”) to 6 (“death”). The outcomes of overall survival and stroke recurrence will be measured with the ICHOM-Standard set for Stroke [11]. The ICHOM-Standard Set for Stroke was developed under the coordination of the International Consortium for Health Outcomes Measurements (ICHOM) and measures a range of patient-reported outcomes from functionality to general health status. Further secondary outcomes are: utilization of health care services, patient’s waiting time between treatment phases, success in regaining target values of relevant risk factors (blood pressure, LDL-cholesterol, HbA1c) and costs. These parameters will be measured via the medical patient record and the rehabilitation portal. Also, a sociodemographic questionnaire will be used, measuring age, gender, living situation, partnership, vascular and non-vascular comorbidities.

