**Methods:**

In this multi-center mixed method sequentially controlled intervention study, stroke patients with ischemic stroke (I63), transient ischemic attack and related syndromes (G45), or intracerebral haermorrhage (I64) will be invited to participate. For a 12-months period, 235 consecutive patients are expected to be enrolled and assigned standard of care treatment as an active control group. During the following 12 months, 235 consecutive patients will be enrolled and assigned to a post stroke intervention program. The StroCare intervention consists of repeated outpatient visits with specialized stroke teams, the implementation of a case manager, the use of an electronical tool for communication between acute care, rehabilitation facilities, and out-patient care, and the definition of individualized treatment targets. Patients will be followed up for 24 months. The primary outcome is health-related quality of life measured by the Patient-Reported Outcomes Measurement Information System 10-Question Short Form (PROMIS-10) at 12 months after the index event, i.e. stroke or TIA. For the qualitative survey of the implementation process, 21 patients in the intervention group will be interviewed after implementation of the interventions. In addition, 20 health care providers and staff members will be interviewed before and after implementation. Additionally, economic outcomes will be evaluated after 6 and 12 months.

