### Study description and study design

The StroCare intervention will be evaluated in a multi-center mixed-methods sequentially controlled intervention study with a longitudinal design (Fig. 1). Onset is acute inpatient stroke treatment with subsequent neurological rehabilitation. Patients will be enrolled during their initial stay at the stroke unit for the control and intervention group during a 12 months period each, starting with the control group. Afterwards, the intervention will be deployed and enrolment in the intervention group will start. For individual patients, the intervention will cover a period of 24 months. The intervention effects on outcomes will be evaluated by a quantitative survey 12 and 24 months after stroke. In terms of the implementation process, qualitative interviews will be conducted with patients after the implementation of the interventions. Additionally, employees (doctors, nurses, and IT staff) involved in the study will be interviewed before and after the implementation of the interventions. Comparative analyses of health-care costs are planned 6 and 12 months after admission with admitted permission to insurance data files. Enrolment of patients in the control group started in January 2020. Scheduled duration of the entire study from first-patient-in to last-patient-out has been extended from 24 to 36 months due to the COVID-19 pandemic.

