### Data analysis

#### Analysis of effectiveness outcomes

The structural equality of the control and intervention groups at baseline will be examined to detect imbalances, using descriptive statistical analysis.

In order to evaluate the intervention effect on the two primary outcomes at the 12-months follow-up, data will be analyzed using linear mixed models. In the fixed part of the model, exposure to the intervention (StroCare vs usual care) will be included as the independent variable of interest. Potential confounding variables will be added as fixed effects in case of baseline imbalance, including demographic characteristics, stroke type and severity of stroke symptoms, as well as vascular and systemic features. The random effects part of the model will include variance parameters for the intercept and for the treatment effect across the participating clinics, respectively. Findings regarding the primary outcomes with an alpha error rate below 0.025 will be considered statistically significant (Bonferroni adjustment for two outcomes).

The primary outcome at the 24-months follow-up and the secondary outcomes will be analyzed using similarly structured models. In the case that data are not normally distributed, generalized mixed models will be applied. Findings regarding the secondary outcomes with an alpha error rate below 0.05 will be considered statistically significant.

Parameter estimates will be reported with 95% confidence intervals. Missing values will be handled using multiple imputation.

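### The text names no enrolment PROMIS-10 and no baseline PROMIS-10 covariate, so a starting difference in quality of life between the sequential groups can be adjusted for only indirectly

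*Protocol article*

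**What the plan says.** Two sections of the protocol article give the timing of the quality-of-life survey, and they agree. The Effectiveness section under Outcome measures says of the patient-reported outcomes: "They will be measured 12, and 24 months after baseline, using the questionnaire" (the PROMIS-10). The section Study description and study design says: "The intervention effects on outcomes will be evaluated by a quantitative survey 12 and 24 months after stroke". The abstract places the primary outcome "at 12 months after the index event, i.e. stroke or TIA".

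The groups are formed by calendar period: "Patients will be enrolled during their initial stay at the stroke unit for the control and intervention group during a 12 months period each", with the control period first.

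The section Analysis of effectiveness outcomes deals with comparability in two steps. The first is a descriptive check of whether the two groups are alike at baseline. The second is conditional adjustment: "Potential confounding variables will be added as fixed effects in case of baseline imbalance". The kinds of variable meant are demographics, the type and severity of the stroke, and vascular and systemic characteristics. No baseline PROMIS-10 or PHQ-4 score is named there.

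Two items leave the schedule less than certain. The Effectiveness section refers to Fig. 3, which is not available here. It also says that "the secondary outcome of depression and anxiety symptoms will be measured at all time points", without listing those time points.

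**The concern.** In a randomised trial, a missing baseline score costs precision but does not bias the comparison. Here comparability has to be shown or modelled. The most direct evidence would be the primary outcome itself, measured before the intervention starts.

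A difference at the start is plausible. Participation depends on consent, and the target of 470 out of about 1200 eligible patients means that roughly 39% take part (470/1200 = 0.392). The two phases also offer different things at consent: usual care in the first, two years of nurse contact and case management in the second. Patients who accept may therefore differ in mental or physical health.

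The adjustment rule adds to the problem. Confounders enter the model only if imbalance is observed, and an imbalance in a variable that was not measured cannot trigger adjustment. Demographics, stroke type and severity stand in only partly for prior health, and least of all for prior mental health, which is one of the two primary scales. A later analysis plan can settle many details, but it cannot adjust for a score that was not collected.

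**Working it through.** **1. The plan's own figure.** Inputs from Sample size calculation: d = 0.3, alpha 0.025, power 80%. Taking the test as two-sided:

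n per group = 2 × (2.2414 + 0.8416)² / 0.3² = 2 × 9.505 / 0.09 = 211.2, so 212.

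The t-test solution is 212.48, which rounds up to the stated 213. The stated 235 is 213 × 1.10 = 234.3, rounded up. The calculation reproduces and uses no baseline score, so the point concerns bias and not the sample size arithmetic.

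**2. Shift from an unadjusted starting gap.** Let b be the difference between groups in baseline PROMIS-10 (in SD) and ρ the correlation of baseline with 12-month score within groups. With a linear relation and equal SDs at both times, the 12-month contrast shifts by ρ × b when the intervention has no effect. The documents give neither b nor ρ. Both are assumed: b = 0.1 to 0.3 and ρ = 0.3 to 0.7.

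**3. Chance of a significant result with no true effect.** With 213 per group, SE = √(2/213) = 0.0969 SD, and P = Φ(ρb/SE − 2.2414) + Φ(−ρb/SE − 2.2414). This is a simple two-group test that ignores clinic effects. For b = 0.2 and ρ = 0.5, ρb/SE = 0.10/0.0969 = 1.032 and P = 11.4%.

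| b | ρ | Shift (SD) | Share of 0.3 | P(significant, no effect) |
|---|---|---|---|---|
| 0.1 | 0.3 | 0.03 | 10% | 3.2% |
| 0.1 | 0.5 | 0.05 | 17% | 4.5% |
| 0.1 | 0.7 | 0.07 | 23% | 6.6% |
| 0.2 | 0.3 | 0.06 | 20% | 5.4% |
| 0.2 | 0.5 | 0.10 | 33% | 11.4% |
| 0.2 | 0.7 | 0.14 | 47% | 21.3% |
| 0.3 | 0.3 | 0.09 | 30% | 9.5% |
| 0.3 | 0.5 | 0.15 | 50% | 24.4% |
| 0.3 | 0.7 | 0.21 | 70% | 47% |

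The nominal rate is 2.5%. With the reference SD of 10 given in the Effectiveness section, the shifts are 0.3 to 2.1 T-score points. A gap in the other direction would hide a true effect by the same amount.

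**4. Precision.** A baseline covariate multiplies the residual variance by 1 − ρ². The 211.2 per group becomes 211.2 × 0.91 = 192.2 (193) at ρ = 0.3, 211.2 × 0.75 = 158.4 (159) at ρ = 0.5, and 211.2 × 0.51 = 107.7 (108) at ρ = 0.7. This assumes that no other covariate already explains part of the outcome.

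**The case against.** A reader might infer that PROMIS-10 is never measured at enrolment. The documents do not say so. The inference rests on silence in the text, while Fig. 3 is not available and the time points for PHQ-4 are not listed. An article may also leave the visit schedule to the full protocol. This stands: the supportable statement is that no enrolment measurement is named. The doubt is limited, however, because both sections that give survey times give the same two.

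A reader might also infer that the design cannot tell an intervention effect from a pre-existing difference, with no means of checking. That goes too far. The plan compares the groups at baseline and adjusts for prognostic factors when they differ, and the covariate list is open-ended. These factors carry some information about prior quality of life. The protection is indirect and conditional, but it exists. It also means that the shifts in the table are those of an unadjusted contrast, not of the planned analysis; adjustment would be expected to shrink them by an unknown amount.

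Finally, an enrolment score has limits. Taken during the acute stay, it reflects the stroke as well as earlier health. In the intervention phase, nurse and case-manager contact begins during acute care, so a late score could follow first exposure. Control enrolment began in January 2020, so controls already in the study may have no score. Nor would the score address calendar-time effects such as the pandemic. All of this stands and shapes the remedy, but it does not remove the gap.

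**Conclusion.** The point holds in limited form. The text schedules the primary outcome at 12 and 24 months only and names no baseline PROMIS-10 term, in a comparison of sequential, non-randomised cohorts. A starting difference in quality of life can therefore be handled only through other variables, and only if those variables look imbalanced.

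The size is illustrative: a shift of 10% to 70% of the target effect across the assumed gaps and correlations, before any adjustment. The documents support none of these inputs, and the true gap could be zero.

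The conclusion depends on Fig. 3 or the full protocol not already providing an enrolment PROMIS-10. If one is provided, what remains is the missing model term and the conditional adjustment rule.

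**What to change.** 1. State in the Effectiveness section whether PROMIS-10 is collected at enrolment, and list the time points for each questionnaire.
2. If it is not collected, add PROMIS-10 and PHQ-4 in both phases, at the same point of the acute stay, with the same recall instruction, and before first contact with the intervention.
3. Prespecify the baseline score of the scale concerned as a fixed effect in each primary model. If the score is already collected, only this term is needed.
4. In either case, replace adjustment triggered by imbalance with unconditional adjustment for pre-stroke status available in both groups. At the least this is premorbid mRS, which the Eligibility criteria already require at screening; it is coarse, since patients with 4 or more are excluded. Add insurer data from before admission if access permits. The article describes insurer data only for costs 6 and 12 months after admission, so this access has to be confirmed.
5. If controls already enrolled lack a baseline score, base the primary adjustment on these shared proxies. Do not use a covariate that is missing mainly in one group, and state that baseline comparability of quality of life is untested for those patients.

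The cost is an amendment, fourteen questionnaire items (ten plus four, a few minutes per patient) and some missing baselines in acutely ill patients. Calendar-time confounding remains and should be named as a limitation.

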### Eligibility criteria

Patients will be included according to the following criteria: treatment at one of the participating acute clinics, diagnosis (ICD-10) of ischemic attack (I63), transient ischemic attack and related syndromes (G45), intracerebral haemorrhage (I64), insurance with the BARMER health insurance agency, sufficient mastery of German language and written informed consent. BARMER insurance membership is necessary due to its cooperation to defray the follow-up examination costs and to give access to patient data. Exclusion is based on the following criteria: premorbid score of mRS≥4, present diagnosis of artificial respiration (Z99.1), dementia (F00.x., F01.x. or G30.x) or aphasia (R47), substantially impaired communication capacity due to aphasia or dementia and admission to a nursing home following the acute treatment.

Patients will be screened by study nurses via electronic health record for diagnosis and insurance company after admission to the stroke unit. They will not be involved in patients´ treatment.

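### Pre-stroke mRS, which is on the same scale as the smRSq outcome, is not a named covariate and could enter the smRSq models only if a baseline imbalance is noticed

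*Protocol article*

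**What the plan says.** All references are to the protocol article.

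- **Eligibility criteria.** One exclusion is a "premorbid score of mRS≥4", so enrolled patients lie between 0 and 3 before the stroke. On how screening is done, the section says: "Patients will be screened by study nurses via electronic health record for diagnosis and insurance company". It does not say whether the premorbid grade is recorded.
- **Outcome measures, Effectiveness.** Among the secondary outcomes, the patient's "functional status will be assessed by the modified Rankin Scale questionnaire (smRSq"). On its range: "The scale of the smRSq ranges from 0", with 6 (death) at the top.
- **Study description and study design.** On timing: "The intervention effects on outcomes will be evaluated by a quantitative survey 12 and 24 months after stroke". On allocation: "Patients will be enrolled during their initial stay at the stroke unit for the control and intervention group during a 12 months period each", with the control period first.
- **Analysis of effectiveness outcomes.** Exposure to the intervention is the fixed effect of interest. On other covariates: "Potential confounding variables will be added as fixed effects in case of baseline imbalance, including demographic characteristics, stroke type and severity of stroke symptoms"; vascular and systemic features complete the list. Secondary outcomes are to have models of similar structure, tested at 0.05.

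**The concern.** Premorbid mRS precedes treatment, is expressed on the outcome's own scale and has to be considered for each patient anyway. Such a variable is normally fixed in the model in advance. Here it is not named, and the general rule makes any adjustment depend on whether an imbalance is noticed.

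Two things are at stake. If premorbid mRS looks balanced, the rule leaves it out and the variance it explains stays in the residual. If it differs moderately between the cohorts, a descriptive comparison may not prompt its inclusion, and part of that difference then carries into the smRSq contrast. Randomisation does not protect against this, because the cohorts follow each other in time. Control enrolment began in January 2020 and the study was extended because of COVID-19, so a change in case mix between the periods is plausible, although the document does not show one.

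**Working it through.** **The plan's own figure.** The only sample size stated is for the PROMIS-10 subscales: d = 0.3, power 80%, alpha 0.025, 213 per group. A two-sided t-test calculation gives 212.5, rounded up to 213, so the figure is reproduced. No effect size or power is stated for the smRSq. Below, n = 213 and d = 0.3 are borrowed as illustrations, with the alpha of 0.05 that the plan sets for secondary outcomes.

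**Is pre-stroke function covered by a named domain?** The domains are "demographic characteristics, stroke type and severity of stroke symptoms, as well as vascular and systemic features". Severity of stroke symptoms describes the index event. The sociodemographic questionnaire covers age, gender, living situation, partnership and comorbidities. None of these is pre-stroke function. The list is introduced as an open one, however, so premorbid mRS is not ruled out.

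**Precision.** Let r be the correlation of premorbid mRS with the later smRSq. It is not in the document, and 0.1 to 0.5 is assumed.

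- Residual variance factor: 1 − r²
- Equivalent n per group without the covariate: 213 / (1 − r²)
- Power (normal approximation, two-sided 0.05): Φ(d × √(213/2) / √(1 − r²) − 1.96)

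Without the covariate and with d = 0.3: 0.3 × √106.5 = 3.096; 3.096 − 1.96 = 1.136; power 87.2%.

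| r | Fall in residual variance | Equivalent n per group | Power at d = 0.3 |
|---|---|---|---|
| 0.1 | 1% | 215 | 87.5% |
| 0.2 | 4% | 222 | 88.5% |
| 0.3 | 9% | 234 | 90.1% |
| 0.4 | 16% | 254 | 92.2% |
| 0.5 | 25% | 284 | 94.7% |

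At d = 0.2, power would be 54.1% without the covariate, 54.6% at r = 0.1 and 66.4% at r = 0.5.

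**Shift if a cohort difference is left unadjusted.** In SD units, shift = r × difference in premorbid mRS. The size of the difference is also an assumption.

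- Difference 0.2 SD: 0.1 × 0.2 = 0.02 to 0.5 × 0.2 = 0.10 SD.
- Difference 0.15 SD: 0.1 × 0.15 = 0.015 to 0.5 × 0.15 = 0.075 SD.

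**Would the imbalance rule catch it?** The article gives a descriptive comparison and no threshold. If a significance test at 0.05 were the screen, z = difference × √(213/2):

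- 0.2 SD: 0.2 × 10.32 = 2.06, just flagged.
- 0.15 SD: 0.15 × 10.32 = 1.55, not flagged.

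On that illustration, a difference somewhat below 0.2 SD would pass unadjusted.

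**The case against.** A reader might infer that premorbid mRS is not used in the analysis at all. The text does not say so. The covariate list is open, and an imbalanced premorbid mRS could enter under the stated rule, so bias is a risk of the rule and not a stated consequence. A large difference would probably be caught: 0.2 SD already gives z of about 2.06.

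A reader might also infer that the graded value is in hand for every patient and then discarded. Eligibility needs only a judgement of below 4 against 4 or more. The screening sentence mentions only diagnosis and insurer, and the figure listing outcome measures is not available. Whether the grade is kept is unknown.

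The size of the gain is uncertain too. Restriction to 0 to 3 may hold r toward the low end, where the gain is negligible. If age, stroke severity or comorbidities are also in the model, the partial correlation matters and may be smaller. The smRSq is ordinal and secondary, so a two-sample comparison of means, which also ignores clinic effects, is only a rough guide.

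Finally, a condensed article may leave its detailed covariate list to an analysis plan. That is fair, and an incomplete list is not the complaint. The point that stands is about the rule the article does state: adjustment that depends on observed imbalance is a poor choice for a prognostic baseline variable on the outcome's own scale in a non-randomised comparison.

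**Conclusion.** The point holds in this limited form. Pre-stroke function is not among the named covariate domains, and the stated rule would admit premorbid mRS only after an imbalance is noticed. That can forgo precision and can leave a moderate pre-stroke difference in the smRSq contrast. The size ranges from negligible (r = 0.1: 1% of residual variance, 0.02 SD shift) to material (r = 0.5: 25% and 0.10 SD, one third of the illustrative d of 0.3). These figures rest on the assumed r, an assumed 0.2 SD cohort difference, and n and d borrowed from the PROMIS-10 planning. No figure in the document is wrong on this point, and the primary analysis is not called into question by it.

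**What to change.** Record the premorbid mRS grade (0 to 3) when eligibility is checked. Prespecify it as a fixed covariate in the smRSq models at 12 and 24 months, regardless of observed balance. The exclusion criterion itself stays as it is.

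The cost is one extra recorded field, if the grade is not already kept, and one model term. If control patients were enrolled without a recorded grade, it should be sought from the same source and in the same way for both cohorts, so that the covariate does not itself differ by period. Adjustment for this variable will not remove other differences between the two periods.
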